# 4 Introduction

## 4.1. Background and Rationale

Cataract is one of the leading causes of low vision in the UK. Cataract surgery is the most commonly performed operation by the NHS with over 310,000 procedures in 2011-12 at an approximate cost of £250 million. The current surgical method introduced over 20 years ago uses ultrasound (phacoemulsification) to help remove the cataract. Following surgery, 91% achieve a Snellen visual acuity of 6/12 or better (the minimum required for driving, 0.30 logMAR) and 46% achieve Snellen 6/6 or better (0.00 logMAR, 20/20 equivalent in the United States, perceived as normal vision.(2) The overall complication rate for cataract surgery is 7.4%.(4) Complications can affect recovery and some are serious and associated with poor long-term outcomes; eg. posterior capsule rupture (PCR)/ vitreous loss (VL) that occurs in ~1.9% cases. Of these one third of patients have complaints about their eye & vision 3.5 years after surgery (5). One in 5 cases need further surgery (6) and there is a 15 times higher risk of retinal detachment within 3 years.(7) The surgical learning curve is associated with complications, with a 3.7 and 1.6 times higher risk of PCR/VL for SHOs and SpRs respectively when compared to Consultants.(8) Other complications, the majority of which are less serious, may mean a longer operation and delayed healing with additional appointments and eye drops. Patients can be devastated when suffering a complication and due to the importance of vision for daily activities, can find even minor complications very distressing.

Laser systems are now available that can make the incisions, open the lens capsule and fragment the cataract in 1 minute, leaving only removal of lens fragments and insertion of the lens implant to be done by the surgeon.

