### 5.5.2 Secondary Outcomes

*Secondary outcomes (all time points relate to times after cataract surgery in the study eye)*

- Uncorrected distance visual acuity (UDVA) at 12 months following surgery on the study eye.
- Corrected distance visual acuity (logMAR) at 3 and 12 months following surgery on the study eye (ETDRS logMAR chart at a starting distance 4 metres).
- Ocular complications within 3 and 12 months of surgery on the study eye. A complication will be defined as any event that causes unintentional injury to an ocular structure, or requires additional treatment, or has a negative effect on a patient's health or eyesight.
- Uncorrected and corrected visual acuity (using the ETDRS chart at a starting distance of 4 metres) and complications in the second eye (for those with bilateral cataracts), and with both eyes open at 3 and 12 months following surgery on the study eye.
- Proportion of patients with vision within 0.5 and within 1 dioptre of intended refractive outcome (and second eye for those with bilateral cataracts) at 3 and 12 months following surgery on the study eye.
- Quality of life as measured by the EQ-5D-3L questionnaire+vision bolt-on question (EQ-5DV) at 6 weeks, 3, 6 and 12 months.
- Patient reported vision health status using Catquest-9SF (26) at 3, 6 and 12 months.
- Cost-utility analysis reported as the incremental cost-effectiveness ratio and cost-effectiveness acceptability curves.
- Corneal endothelial cell count (additional safety measure) in both eyes, at 3 and 12 months following surgery on the study eye.

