#### 5.10.4.2 Statistical Methods – Outcomes

The primary outcome is uncorrected distance visual acuity at 3 months following surgery on the study eye, measured using an ETDRS chart at a starting distance of 4 metres. Mean UDVA will be reported together with a two-sided 95% confidence interval. This will be compared between treatment groups using regression analysis adjusting for baseline habitual logMar^[[1]](#footnote-2)^ visual acuity and the randomisation stratifiers (treatment centre, surgeon, and whether or not patients have one or both eyes eligible). We will include trial site in our regression models as a fixed effect and surgeon as a random effect. If the upper end of the 95% CI for the difference between means does not cross the non-inferiority limit of 0.1 logMAR, then laser surgery will be regarded as non-inferior. If the mean difference is negative and its 95% CI lies wholly to the left of zero, then we can conclude that laser surgery is superior to manual surgery. We will perform sequential testing of the non-inferiority and superiority hypotheses.

Secondary continuous outcomes such as uncorrected distance visual acuity at 12 months, corrected distance visual acuity and patient reported outcome measures Catquest-9SF will be analysed in a similar fashion. The percentage of study eyes experiencing adverse events (e.g. posterior capsule tears, dropped lens) in the two groups will be compared using Fisher’s exact tests.

In addition regression analyses will be performed for continuous outcomes such as corrected distance visual acuity at 12 months for the study eye, adjusting for baseline habitual logMar visual acuity and the randomisation stratifiers (treatment centre, surgeon, and whether or not patients have one or both eyes eligible). Baseline habitual logMar visual acuity is only collected for the study eye and therefore distance visual acuity outcomes for the fellow eye, whether they are unaided or corrected, will only be adjusted for the randomisation stratifiers.

Pearson’s correlation coefficients (or Spearman’s rank correlation coefficients, depending on the distribution of the data) will be used to assess the relationships between the continuous objective and subjective outcome measures.

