### 5.11.3 Data Monitoring for Harm

#### 5.11.3.1 Safety reporting

Definitions of harm of the EU Directive 2001/20/EC Article 2 based on the principles of ICH GCP apply to this trial.

Table 2: Adverse Event Definitions

| **Adverse Event (AE)** | Any untoward medical occurrence in a study participant which does not necessarily have a causal relationship with the treatment under study e.g. abnormal laboratory findings, unfavourable symptoms or diseases. |
| --- | --- |
| **Serious Adverse Event (SAE)** | Any AE that :   - results in death - is life threatening* - requires hospitalisation or prolongs existing hospitalisation** - results in persistent or significant disability or incapacity - is a congenital anomaly or birth defect - or is another important medical condition*** |
| **Suspected Unexpected Serious Adverse Event** | A serious adverse event, the nature or severity of which **is not consistent** with the known potentially **expected** events associated with the applicable trial treatment. The event is evaluated as having a possible, probable or definite relationship to a trial treatment **and** is unexpected for that trial treatment. |
| * the term life threatening here refers to an event in which the patient is at risk of death at the time of the event; it does not refer to an event that might hypothetically cause death if it was more severe (eg a silent myocardial infarction)  ** Hospitalisation is defined as an in-patient admission, regardless of length of stay, even if the hospitalisation is a precautionary measure for continued observation. Hospitalisation for pre-existing conditions (including elective procedures that have not worsened) do not constitute an SAE  *** Medical judgement should be exercised in deciding whether an AE is serious in other situations. | |

Adverse events include:

- an exacerbation of a pre-existing illness
- an increase in the frequency or intensity of a pre-existing episodic event or condition
- a condition (regardless of whether PRESENT prior to the start of the trial) that is DETECTED after surgery. (This does not include pre-existing conditions recorded as such at baseline.)
- continuous persistent disease or a symptom present at baseline that worsens following surgery

Adverse events do NOT include:

- Medical or surgical procedures: the condition that leads to the procedure is the adverse event
- Pre-existing disease or a condition present before treatment that does not worsen

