##### 5.11.3.5.4 Expectedness

If there is at least a possible involvement of the trial intervention (including any comparators), the investigator and sponsor must assess the expectedness of the event. An unexpected adverse event is one that is not reported in the current literature, or one that is more frequently reported or more severe than previously reported. See below for a list of expected complications associated with the procedures being used in this trial.

Expected intraoperative complications for **both** arms include all those common to phacoemulsification cataract surgery:(2)

- Anterior capsule tear
- Posterior capsule tear with or without vitreous loss
- Choroidal effusion/ haemorrhage
- Zonular Dialysis
- Intra-operative pupil constriction needing intervention
- Dropped lens fragments or nucleus

Expected trial complications specifically for the **laser assisted** arm:

- Failure to dock to laser
- Aborted or incomplete laser delivery
- Incomplete capsulotomy identified in surgery, requiring manual completion
- Laser delivery to Inappropriate structure of eye

Expected post-operative complications for **both** arms:

- Post-operative uveitis
- Endophthalmitis
- Macular oedema
- Retinal tear or retinal detachment
- Elevated intraocular pressure requiring treatment
- Medication allergy or intolerance
- Corneal oedema
- Vitreous to wound
- Other ocular surgery

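### The safety test uses a different event term from the defined complication outcome, is an unadjusted Fisher test, and yields no between-arm estimate

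*Protocol*

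**What the plan says.** The analysis sentence in section 5.10.4.2 reads: "The percentage of study eyes experiencing adverse events (e.g. posterior capsule tears, dropped lens) in the two groups will be compared using" Fisher's exact tests. It gives no time window, adjustment or effect measure. Section 5.10.4.1 promises proportions and percentages for binary data, but no interval for the difference between arms.

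Section 5.5.2 defines the safety outcome in other terms: "Ocular complications within 3 and 12 months of surgery on the study eye". It adds: "A complication will be defined as any event that causes unintentional injury to an ocular structure, or requires additional treatment", or harms the patient's health or sight. In section 5.11.3.1 an adverse event is wider: "Any untoward medical occurrence in a study participant which does not necessarily have a causal relationship with the treatment under study".

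Laser events appear in two places:
- Section 5.11.3.3 puts laser faults that prevent delivery under its heading for notifiable adverse events.
- Section 5.11.3.5.4 lists four expected complications for the laser arm alone: failed docking, aborted or partial delivery, "Incomplete capsulotomy identified in surgery, requiring manual completion", and laser energy reaching the wrong part of the eye.

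On surgeons, section 5.9.1.1 minimises by centre, surgeon and one or both eyes. Section 5.7 says patients within a surgeon are not independent. The continuous outcomes are adjusted for these factors, with surgeon as a random effect. Section 4.1 reports that training grade matters, "with a 3.7 and 1.6 times higher risk of PCR/VL for SHOs and SpRs respectively when compared to Consultants".

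**The concern.** Ocular complications are one of the four questions in section 4.2, yet the planned comparison is loosely tied to the defined outcome in three ways.

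1. **The event set is not fixed.** The tested term is broader than the defined one and lacks the 3- and 12-month windows. The protocol files laser non-delivery under adverse events or complications without saying whether it enters the comparison. Complications are reviewed by an unmasked team member (section 5.9.2), so this should not be left to judgement.
2. **The test ignores the design.** It does not use surgeon, although surgeon is a minimisation factor and section 5.7 rests on clustering by surgeon. Fisher's test is also conservative at these event rates.
3. **No estimate is named.** A non-significant p-value does not show how large an excess of harm has been excluded, which is what readers of a non-inferiority trial need.

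**Working it through.** **The plan's own figure.** Section 5.7 gives no figure for safety, so the arm size comes from the primary outcome.
- n per group = 2 × (1.960 + 1.282)² × 0.32² / 0.1² = 215.2, so 216, or 432 in total.
- f = 1 + 49 × 0.012 = 1.588.
- 432 × 1.588 = 686.0, or 688 when rounded up per arm.
- 688 / 0.85 = 809.4, and 432 × 1.59 / 0.85 = 808.1, against 808 stated.

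The stated size reproduces within rounding: 404 per arm, or 344 after dropout.

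**Event rates.** Section 4.1 gives 7.4% for overall complications and about 1.9% for capsule rupture or vitreous loss.

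**True size of Fisher's test.** Two binomials with equal rates were enumerated exactly (two-sided, nominal 5%).

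| Rate in both arms | 404 per arm | 344 per arm |
| --- | --- | --- |
| 7.4% | 3.8% | 3.5% |
| 1.9% | 2.7% | 2.4% |

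**Stratifying by surgeon.** The simulation used 20,000 runs, 16 surgeons and 25 patients per arm per surgeon (400 per arm), with one treatment odds ratio for all surgeons. The assumed mix is 8 consultants, 5 SpRs and 3 SHOs at relative risks 1, 1.6 and 3.7. The mean relative risk is (8 + 8 + 11.1)/16 = 1.694. A 7.4% average therefore means 4.4%, 7.0% and 16.2% by grade. Applying capsule-rupture risk ratios to all complications is a further assumption.

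| | Fisher | Unadjusted chi-square | Mantel-Haenszel by surgeon |
| --- | --- | --- | --- |
| 7.4%, type I error | 3.6% | 4.9% | 5.1% |
| 7.4%, power at odds ratio 0.5 | 52.3% | 57.6% | 58.8% |
| 1.9%, type I error | 2.8% | 4.7% | 5.1% |
| 1.9%, power at odds ratio 0.5 | 12.4% | 18.0% | 18.9% |

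At 7.4% the gain is 58.8 − 52.3 = 6.5 points. Of this, 57.6 − 52.3 = 5.3 come from leaving Fisher's discreteness behind and 1.2 from stratification.

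**If the treatment effect varies by surgeon.** Section 5.7 describes clustering this way. If f = 1.588 carried over to safety (assumption), the error is 2 × (1 − Φ(z/√1.588)). That is 12.0% for a test of true size 5% (z = 1.960), 9.9% for Fisher at a 7.4% rate (z = 2.079) and 7.9% at 1.9% (z = 2.213). Mantel-Haenszel does not remove this inflation.

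**Laser-only events.** Suppose the true rate is 7.4% in both arms, all such events are counted in one composite, and a proportion d of laser eyes has one independently. The laser-arm rate is 1 − 0.926 × (1 − d). The protocol gives no value for d.

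| d | Laser-arm rate | False result against laser, 404 per arm | 344 per arm |
| --- | --- | --- | --- |
| 0 | 7.4% | 1.9% | 1.8% |
| 1% | 8.3% | 5.6% | 4.9% |
| 2% | 9.3% | 13% | 11% |
| 3% | 10.2% | 25% | 21% |

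If laser truly halved complications (7.4% to 3.7%), the chance of a significant result at 404 per arm would fall from 58% at d = 0 to 32%, 14% and 6% at d = 1%, 2% and 3%.

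**What an interval would add.** With 7.4% in both arms, the 95% half-width for the risk difference is 1.96 × √(2 × 0.074 × 0.926 / 404) = 3.6 percentage points (3.9 at 344 per arm). A null result would still allow an excess of nearly half the baseline rate, which a p-value does not show.

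**The case against.** The strongest reply is that this is a matter of wording. The unit is the study eye, and both examples are ocular complications listed in section 5.11.3.5.4, so the 5.5.2 outcome was probably meant. That stands. A reader might infer that the defined outcome has been replaced by another; the text shows unreconciled terms, not a replacement.

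A reader might also infer an any-event percentage loaded against laser by construction. The protocol does not say so. The plural tests may mean one per event type, section 5.11.3.5.4 serves safety reporting and does not define an outcome, and a failed docking followed by manual surgery need not be a complication under 5.5.2. The laser-event results above are therefore conditional. What remains is that nothing states whether these events count.

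Nor does the grade effect in section 4.1 show confounding. Minimisation is expected to balance surgeons between arms, the protocol does not say that SHOs will operate, and unadjusted chi-square performs almost as well as the stratified test.

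An exact test is an ordinary choice for rare events, and conservatism is not an error. For capsule rupture at 1.9% against 0.31%, about 8 events against 1, Fisher should stay, so its 47% power there is no argument for replacing it.

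Finally, event lists and effect measures are often left to a SAP. That is fair, but the protocol has already fixed the test and the term, and they do not match its own outcome definition.

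**Conclusion.** The concern holds in a limited form and merits correction before analysis. The protocol's safety comparison does not name its own defined outcome or time windows, leaves surgeon out despite minimising on it, and commits to no between-arm estimate.

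The cost of Fisher's test for overall complications is modest: a true size of about 3.8% rather than 5%, and roughly 6 to 7 points of power at an odds ratio of 0.5. This rests on the assumed surgeon mix and a common treatment effect, and most of it is discreteness. The open question of laser-only events could matter more, with a false result against laser in 13–25% of trials instead of 1.9%, but only if a composite counts them and 2–3% of laser eyes are affected. Neither condition is stated in the protocol.

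A reader might conclude that the comparison should be limited to events possible in both arms. The documents do not support that. Laser delivery to the wrong part of the eye can occur only in arm B, yet it meets the 5.5.2 definition as an injury to the eye. Dropping it would bias the comparison towards laser.

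**What to change.** In section 5.10.4.2:
- Name the section 5.5.2 ocular-complication outcome in the study eye, within 3 and within 12 months.
- Compare the overall rate by Mantel-Haenszel stratified by surgeon, or by mixed logistic regression with the randomisation stratifiers. Report a risk difference or odds ratio with 95% CI.
- Keep Fisher's exact test for single event types too rare to model.
- Apply the 5.5.2 definition equally to both arms, so that eye injury caused by the laser still counts. Tabulate separately, for arm B, device or delivery failures that do not meet it.
- Before analysis, state which laser-arm items in sections 5.11.3.3 and 5.11.3.5.4 meet the definition. Manual completion of a capsulotomy needs an explicit ruling, because it could be read as additional treatment.

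The cost is a few sentences, a little more analysis and a pre-stated fallback for sparse strata or a model that fails to converge. Stratification will not deal with a treatment effect that varies between surgeons; if that is thought likely for complications, a sensitivity analysis allowing for it can be added.

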## 5.6 Participant Timeline

**Figure 1: Schedule of Assessments**

|  | Standard pre-assessment (for study and non-study patients) | **Baseline** | **Randomisation** | **Follow up** | | | | |
| --- | --- | --- | --- | --- | --- | --- | --- | --- |
|  |  | Surgical Pre Assessment Visit | Randomisation and surgery | Standard non-study post-op appt | 6 weeks post-surgery (by post)  (ideally +/-14 days) | 1^st^ trial apt: 3 months post-surgery  (ideally +/-14  days) | 6 months post-surgery  (by post)  (ideally+/-14  days) | 2^nd^ trial apt: 12 months post-surgery  (ideally +/-14 days) |
| Visit Number | *1* | *1 or later* | 2 | *3* |  | *4* |  | *5* |
| Past medical and ocular history | X | X |  |  |  |  |  |  |
| Consent for cataract surgery | X |  |  |  |  |  |  |  |
| Informed Consent & eligibility screening |  | X |  |  |  |  |  |  |
| Identification of study eye |  | X |  |  |  |  |  |  |
| Visual acuity: UDVA, pinhole, +/- glasses (Snellen), each eye | X |  |  | X |  |  |  |  |
| Visual Acuity: UDVA^1^ & CDVA^2^ (logMAR) each eye and binocular |  |  |  |  |  | X |  | X |
| Visual acuity (LogMAR) with usual method of correction |  |  | X^7^ |  |  |  |  |  |
| Subjective refraction |  |  |  |  |  | X |  | X |
| Ocular biometry | X |  |  |  |  |  |  |  |
| Pentacam corneal topography | X^6^ | X |  |  |  | X |  | X |
| Optical coherence tomography (OCT)^3^ | X^6^ | X^8^ |  | X^6^ |  | X |  | X |
| Inclusion/Exclusion Criteria |  | X |  |  |  |  |  |  |
| Catquest-9SF questionnaire |  | X |  |  | X | X | X | X |
| EQ-5D-3L+vision bolt-on question (EQ-5DV) |  | X |  |  | X | X | X | X |
| CSRI^5^ |  | X |  |  |  | X | X | X |
| Endothelial cell count measurement | X^6^ | X^8^ |  |  |  | X |  | X |
| Surgery |  |  | X |  |  |  |  |  |
| Adverse Event Collection |  |  |  |  | X | X | X^4^ | X |

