*^1^UDVA: uncorrected distance visual acuity. All visual acuity measures will use the standard ETDRS logMAR chart at 4 metres. At the baseline visit (usual pre-assessment clinic for cataract surgery) ETDRS will be the usual care visual acuity measure and thus can be taken prior to consent, ^2^CDVA: corrected distance visual acuity using subjective refraction result .^3^OCT will be measured as part of the standard pre-assessment for all patients. OCT will be repeated at 3 and 12 months. ^4^patient reported complications only. ^5^The Client Service Receipt Inventory (CSRI) is a questionnaire for collecting retrospective information about study patients’ use of health and social care services, accommodation and living situation, income, employment and benefits.(28) ^6^Some patients will have these tests performed at the standard pre-assessment visit, depending on the site local procedure for surgical pre-assessment. ^7^Current glasses or unaided. ^8^ baseline procedures which should be repeated if surgery is delayed for more than 3 months.*

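### Fellow-eye acuity models use no baseline although each-eye acuity is scheduled before randomisation, and Figure 1 and its footnote disagree on the chart and visit for baseline acuity

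*Protocol*

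**What the plan says.** Section 5.10.4.2 compares 3-month uncorrected acuity in the study eye by regression on baseline habitual logMAR acuity and the stratifiers (centre, surgeon, one or both eyes). Its footnote defines habitual acuity as logMAR acuity with current glasses or unaided. For the fellow eye the section drops the baseline term because "Baseline habitual logMar visual acuity is only collected for the study eye", so those outcomes "will only be adjusted for the randomisation stratifiers". Second-eye acuity at 3 and 12 months is a listed secondary outcome (section 5.5.2).

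Figure 1 (section 5.6) has two rows for acuity before surgery:

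- "Visual acuity: UDVA, pinhole, +/- glasses (Snellen), each eye" is marked at standard pre-assessment and again at the routine post-operative appointment.
- "Visual acuity (LogMAR) with usual method of correction" has a single mark, in the Randomisation and surgery column, and names no eye.

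No acuity row is marked in the column headed Baseline.

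Footnote 1 to Figure 1 says "All visual acuity measures will use the standard ETDRS logMAR chart at 4 metres". It then equates the baseline visit with the pre-assessment clinic and adds that "ETDRS will be the usual care visual acuity measure and thus can be taken prior to consent".

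**The concern.** Two things look wrong.

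First, the reason for leaving baseline acuity out of the fellow-eye models is that one particular measure is unavailable. The schedule shows another acuity measure in the same eye before randomisation, and section 5.10.4.2 does not say why it is not used. Baseline acuity is an obvious candidate covariate for an acuity outcome. Leaving it out gives up precision and protection against chance imbalance.

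Second, the table and the footnote give different answers on which chart is used at pre-assessment and when baseline logMAR acuity is recorded. This reaches beyond the fellow eye, because habitual logMAR acuity is the baseline covariate of the primary non-inferiority model. Surgery typically follows enrolment by 4 to 8 weeks (section 5.4.3), so a pre-assessment reading and a surgery-day reading are not the same variable. Randomisation also takes place on the day of surgery (sections 5.4 and 5.9.1.2), so a surgery-day covariate needs a stated place in the order of events.

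**Working it through.** **1. The passages side by side**

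| Question | Figure 1, table | Figure 1, footnote 1 | Section 5.10.4.2 |
|---|---|---|---|
| Chart at pre-assessment | Snellen | ETDRS | not stated |
| Visit for baseline logMAR acuity | Randomisation and surgery | pre-assessment clinic | called baseline, no visit named |
| Eyes, pre-assessment acuity | each eye | not stated | not mentioned |
| Eyes, habitual logMAR acuity | not stated | not stated | study eye only |

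There are two ways to read this:

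- *The table governs.* Pre-assessment acuity is Snellen in each eye. The statement in section 5.10.4.2 about habitual logMAR can then stand, but a convertible fellow-eye baseline exists and is not used.
- *The footnote governs.* Pre-assessment acuity is on the ETDRS chart. Combined with the table's each-eye, with-or-without-glasses row, this would give habitual logMAR acuity for both eyes, contrary to section 5.10.4.2.

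Either way a fellow-eye acuity is scheduled before randomisation. It also precedes first-eye surgery, so it is a proper baseline for a comparison randomised at the first eye.

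**2. The plan's own figure**

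The fellow-eye model rests on no stated figure. The sample size in section 5.7 uses no baseline covariate and is unaffected. It reproduces from its inputs (margin 0.1, SD 0.32, 90% power, two-sided 95% interval):

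- n per group = 2 × (1.960 + 1.282)² × 0.32² / 0.1² = 215.2, rounded up to 216, total 432 as stated.
- Design effect 1 + 49 × 0.012 = 1.588. 432 × 1.588 = 686.0, or 686.9 with 1.59 (stated 688).
- 686.0 / 0.85 = 807.1, rounded up to 808 as stated (688 / 0.85 would give 810).

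**3. What a fellow-eye baseline would buy**

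Let r be the correlation between fellow-eye baseline and follow-up acuity. The protocol gives no value, so r is an assumption. Residual variance is multiplied by 1 − r², and hence:

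- reduction in standard error = 1 − √(1 − r²)
- equivalent increase in patients = 1/(1 − r²) − 1

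| Assumed r | 1 − r² | SE reduction | Equivalent extra patients |
|---|---|---|---|
| 0.2 | 0.96 | 2.0% | 4% |
| 0.3 | 0.91 | 4.6% | 10% |
| 0.4 | 0.84 | 8.3% | 19% |
| 0.5 | 0.75 | 13.4% | 33% |

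**4. The same on the logMAR scale**

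Further assumptions: 688 evaluable patients, SD 0.32 as in section 5.7, clustering ignored, and 30%, 50% or 70% of patients contributing a second eye (the share is not in the protocol). With m = 688 × share / 2 per arm, the 95% half-width is 1.96 × 0.32 × √(2/m) × √(1 − r²).

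| Share | r = 0 | r = 0.2 | r = 0.5 |
|---|---|---|---|
| 30% | 0.0873 | 0.0855 | 0.0756 |
| 50% | 0.0676 | 0.0663 | 0.0586 |
| 70% | 0.0572 | 0.0560 | 0.0495 |

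The largest gain shown is 0.0873 − 0.0756 = 0.0117 logMAR, about 0.6 of a letter at 0.02 logMAR per letter.

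**The case against.** The best reply is that section 5.10.4.2 speaks only of habitual logMAR acuity, while the each-eye row is Snellen, so the two can both be true. In the table, marker 1 is attached to the UDVA entry of the 3- and 12-month logMAR row, not to the Snellen row. This stands: a reader might infer that section 5.10.4.2 is false, and on the table's reading it is not. It still leaves an available covariate unused, and the footnote's own text is about the baseline visit, so the conflict over chart and visit remains.

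The pre-assessment column covers study and non-study patients alike, and nothing says the fellow-eye values reach the CRF. This also stands and bears on cost. Section 5.10.5 does, however, already plan to extract routine post-operative acuity from patient records for all patients, so the route exists.

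The gain may be small. Second-eye surgery is planned about 2 to 8 weeks after the first (section 5.4.3), so most second eyes should have been operated on before 3 months, and acuity after cataract removal need not follow acuity before it. This is why correlations above 0.5 are not used here.

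A reader might also infer that the fellow-eye analysis is biased, or that the primary covariate is read after allocation or in a dilated eye. The documents support neither. Leaving a baseline covariate out of a randomised comparison costs precision and does not in itself bias it. Figure 1 marks visits, not the order within a visit, and no passage puts the reading after allocation or dilation. Preparation for surgery is the same in both arms (section 5.4.2.1), so any effect of dilation should be similar in each. What remains is that the order is not stated. Order within a visit is often fixed in a CRF or SAP, but the conflict over visit and chart is in the protocol itself.

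**Conclusion.** The point holds as two modest findings.

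- **Fellow eye.** A baseline acuity scheduled before randomisation is not used. The loss is about 2% to 13% of the standard error for an assumed correlation of 0.2 to 0.5, in a secondary outcome. The planned analysis remains valid.
- **Baseline acuity generally.** The table and footnote 1 contradict each other on the pre-assessment chart and on the visit at which logMAR acuity is taken. This matters more than the fellow-eye precision, because it leaves the primary model's covariate without one clear definition. No numerical consequence for the primary result can be derived from the protocol, and none is claimed.

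**What to change.** - Reconcile Figure 1, its footnote 1 and section 5.10.4.2 so that they name one visit, one chart and the eye or eyes for baseline acuity.
- State that the covariate of the primary model is read before randomisation.
- Adjust fellow-eye acuity models for the pre-assessment fellow-eye acuity: ETDRS if the footnote is right, otherwise Snellen converted to logMAR. Take it from the CRF, or from routine records by the route section 5.10.5 already sets out for post-operative acuity. If it is not to be used, say why.
- Do not substitute the pre-assessment reading for a missing primary covariate unless the chart is the same. Otherwise converted Snellen and ETDRS values, typically weeks apart, would be mixed in one variable.

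The cost is wording in three places, plus record extraction if fellow-eye values are not on the CRF. A converted Snellen value is a coarser covariate, which would reduce the gain. No new test is needed and the sample size does not change.
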